#### Trial flow

The RCT consisted of three regular clinical visits at zero, three, and six months (see Figure 5). Patients in the control group simply had regular visits with their providers and were given a brochure about prediabetes before each visit. For patients in the intervention group, prior to each visit, the brief goals-elicitation questionnaire was administered. These data were then entered into the EHR so that the baseline level of the activity and diet goal was displayed to the provider. During the visit, the ADAPT tool was launched (if selected by the provider), and the action plans were negotiated between patient and provider. The providers had the option of using the behavior-change prop of their choice, and afterwards, the patient was given the behavior-change sample. Between each visit with their provider, patients in the intervention group received an email with a web link for an implementation-intention exercise two days after the visit, weekly behavior change tips, and biweekly web forms to record their average steps per day and self-reported level of their diet goal. Once patients have entered their data about their number of steps and diet behaviors, they see a screen displaying their progress over time and in relation to other study participants (see Figure 6). These activities are repeated at each visit, and after six months, both control and intervention patients are mailed home a pedometer to wear for another one week, after which they return it as well as complete a closeout survey.

**Figure 6 F6:**
[figure not shown]
**Screenshot of ADAPT website feedback display**. ADAPT = Avoiding Diabetes Thru Action Plan Targeting.

### Measures

#### Baseline

##### Patient level

Patient characteristics, including age, gender, body mass index, hemoglobin A1C, lipid levels, and medications are captured via EHR chart review. A baseline patient survey based on validated survey instruments assesses the following domains: demographics, medical history, health status [31], physical activity [32], diet [33], family history, prediabetes knowledge, diabetes risk perception [34], weight history [32], social support [32], depression [35], anxiety [36], stage of change [16], and locus of control [37].

##### Provider level

Provider characteristics, including age, gender, years of practice, and attitudes towards prediabetes counseling, are captured via self-report.

### Follow-up

#### Patient level

##### Three month

Intervention and control patients will have fasting preserved glucose and hemoglobin A1C measured.

##### Six month

Intervention and control patients complete a slightly modified version of the baseline survey after their six-month visit (excluding static components such as demographics). Intervention patients also complete a brief survey on their impression of the ADAPT tool components. The pedometer is then mailed home again, and the patients are instructed to wear it for another week and then mail it back to the study team.

#### Provider level

##### Six month

Intervention and control providers are again surveyed about their attitudes towards prediabetes counseling. Intervention providers only are also surveyed about their impression of the ADAPT tool components.

##### Process outcomes

The process outcomes are designed to assess the utilization of the ADAPT tool components by providers and patients. This is a critical outcome because poor provider utilization of clinical decision support and other evidence-based medicine and quality improvement tools have been a frequent barrier to their success [38]. Measured markers of utilization include rate of accepting the ADAPT tool in eligible patients, using the goal-setting flowsheet, and use of the bundled order set linked to the goal-setting activity.

##### Outcome

The outcome measurements are designed to detect changes in patient behaviors that are most likely to result from use of the ADAPT tool. The primary outcome is the difference between intervention and control patients in the change in mean steps per day at baseline and after six months (a difference of differences). Secondary outcomes include the six-month difference of differences in hemoglobin A1C and self-reported diet between the two groups.

##### Data monitoring and quality control

Weekly reports are generated to track the frequency of the tool triggering, including the use of each component of the ADAPT EHR components and the website. Periodic chart reviews are conducted to monitor the appropriateness of tool triggering and to investigate any concerns raised by providers regarding usability or workflow disruptions.

### Statistical analysis

The primary outcome for this pilot randomized control trial will be the change in physical activity as measured in steps/day at six months among prediabetes patients randomized to providers using the ADAPT system compared to those seeing providers in the control arm. We will use descriptive statistics to summarize the variables and detect outliers, data entry mistakes, and missing values. Intervention- and control-group differences in physical activity changes (pre - post) will be tested using a t-test or Wilcoxon test as appropriate, depending on the normality of the data. To further test the effect of ADAPT, we will use a generalized estimating equation model with clinician as the cluster variable, mean difference in steps/day as the outcome variable, and intervention group as the only explanatory variable. Given the nature of the possible relationship between patients in a cluster, we will use an exchangeable correlation structure for parameter estimation. Secondary analysis will use the same methods to examine differences in hemoglobin A1C and diet between those receiving the intervention versus control. Additional analyses accounting for baseline variables will be performed using generalized linear models. If appropriate, missing data will be accounted for using multiple imputation methods.

As this is a pilot RCT, it is underpowered to detect anything but an extremely large change in the primary outcome of physical activity. Based on pilot resources, we designed the pilot trial with a sample size of 60 patients (30 intervention and 30 control) as this provides us 49% power to detect a difference of the recommended physical activity change goal (2000 steps; standard deviation = 3649) [39,40].

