#### Provider eligibility, consent, and randomization

All attending-level primary care providers who have seen at least 10 patients with prediabetes in the prior year in the medical practice are eligible for the study. The study design is a randomized control trial (RCT) in which the providers within the academic medical center outpatient practice are the unit of randomization. Faculty providers are randomized via random number generator to intervention or control in a 1:1 ratio. Only providers randomized to the intervention are triggered by the EHR to use the ADAPT tool when enrolled patients arrive for a visit. After randomization, all intervention-group providers are invited to standardized educational forums for consent and training on use of the EHR-embedded ADAPT tool (see Figure 5 for a diagram of the study flow). Randomization began in November 2011, with 20 primary care providers being enrolled. Patient recruitment is ongoing with an expected completion date of approximately one year.

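### Providers were randomised, but the first test listed for the primary outcome treats patients as independent, and no analysis is named as decisive

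*Protocol article*

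**What the plan says.** Under Provider eligibility, consent, and randomization, the protocol article states that "the providers within the academic medical center outpatient practice are the unit of randomization", allocated 1:1, and reports: "Randomization began in November 2011, with 20 primary care providers being enrolled".

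Under Outcome it states: "The primary outcome is the difference between intervention and control patients in the change in mean steps per day", from baseline to six months.

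The Statistical analysis section then sets out these steps:

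- The between-group difference in pre–post change "will be tested using a t-test or Wilcoxon test as appropriate, depending on the normality of the data". No provider term is mentioned.
- A second analysis follows: "To further test the effect of ADAPT, we will use a generalized estimating equation model with clinician as the cluster variable". It has an exchangeable working correlation, and treatment group is the only explanatory variable.
- HbA1c and diet are to be analysed by the same methods.
- "Additional analyses accounting for baseline variables will be performed using generalized linear models". Whether these models keep a clinician term is not said.
- The planned size is 60 patients, 30 per arm.

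The section does not rank the first two analyses, and it gives no ICC or design effect.

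**The concern.** When providers are allocated, patients of one provider share both the allocation and whatever makes that provider's patients alike. A t-test or Wilcoxon test on 60 patients takes them as 60 independent units. If outcomes within a provider are positively correlated, the standard error is too small and the test rejects too often. The article itself expects such correlation, since it chooses an exchangeable structure for patients of the same clinician.

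Two things are at stake. First, a stated analysis of the primary outcome, and of both secondary outcomes, does not hold its nominal level for any positive ICC. Second, two tests of one outcome stand side by side with no rule for when they disagree, so a reader of the results could not tell which p-value was meant to count.

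**Working it through.** **Inputs from the article.** 20 providers, 1:1, so about 10 per arm. 60 patients, 30 per arm, so 60/20 = 3 per provider on average. Effect 2000 steps, SD 3649, stated power 49%.

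**Assumed, because not given.** Two-sided 5% level; ICC of the change in steps from 0 to 0.20; the spread of patients over providers.

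**The plan's own figure.** With 30 per arm the standard error is 3649 × √(2/30) = 942, so the standardised effect is 2000/942 = 2.12. Power is Φ(2.12 − 1.96) ≈ 56.5%, or 55.1% with the t distribution. The stated 49% is not reproduced. It matches 25 per arm (49.1%). That would fit a design effect of 30/25 = 1.2 or about 17% dropout, but the article gives neither. The point below does not depend on this figure.

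**Type I error of the patient-level t-test, equal clusters.** The design effect is DE = 1 + (3 − 1) × ICC, and the true size is 2 × [1 − Φ(1.96/√DE)]. The naive standard error is 1/√DE times the correct one.

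**Uneven clusters.** As an illustration, take 1, 1, 1, 1, 2, 2, 3, 4, 6 and 9 patients per provider in each arm. The sum is 30 and the sum of squares is 154, so DE = 1 + (154/30 − 1) × ICC = 1 + 4.13 × ICC.

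The simulated columns use 10 providers and 30 patients per arm, normal data and 40,000 runs.

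| ICC | DE, equal | Size by formula, equal | Naive SE / correct SE | t-test simulated, equal | t-test simulated, uneven | Provider-mean t-test simulated, equal / uneven |
|---|---|---|---|---|---|---|
| 0.01 | 1.02 | 5.2% | 0.99 | 5.3% | 5.3% | 5.0% / 4.7% |
| 0.05 | 1.10 | 6.2% | 0.95 | 6.3% | 7.3% | 5.0% / 4.8% |
| 0.10 | 1.20 | 7.4% | 0.91 | 7.4% | 9.8% | 4.9% / 4.8% |
| 0.20 | 1.40 | 9.8% | 0.85 | 9.8% | 14.8% | 4.8% / 4.8% |

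The Wilcoxon test behaves alike (10,000 runs): 5.2%, 6.1%, 6.7% and 9.6% with equal clusters. The uneven pattern above is strong. Milder patterns (coefficient of variation of cluster size about 0.65) gave about 13–14% at ICC 0.20.

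**The GEE as a replacement.** Simulations of an exchangeable GEE with an uncorrected sandwich variance and a normal reference gave about 7–8.5% with equal clusters and 11–14% with uneven ones. The excess is present at ICC 0. In one set of 1,500 runs at ICC 0, with sizes from 1 to 8, the GEE rejected 7.4% (equal) and 14.3% (uneven), against 4.7% and 5.3% for the t-test. The cause is the small number of clusters, not the correlation.

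**Power of the provider-mean test.** For 2000 steps with equal clusters and 18 degrees of freedom: 52%, 48%, 45% and 40% at ICC 0, 0.05, 0.10 and 0.20.

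**The case against.** The strongest reply is that clustering is not overlooked. The same section plans a GEE on clinician, and by extension applies it to HbA1c and diet. The article calls the trial a pilot, concedes that it is underpowered, and may leave the choice of deciding analysis to a fuller plan. With 3 patients per provider the inflation is small unless the ICC is sizeable, and up to ICC 0.05 the t-test lies closer to 5% than an uncorrected GEE does.

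Much of this stands, and it rules out several stronger readings that a reader might infer:

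- *The plan ignores clustering.* It does not; the GEE is there.
- *The t-test is the designated primary test.* The article only lists it first and calls the GEE a further test. It ranks neither.
- *Having two tests is what drives the false-positive rate.* Counting success on either test gave 7.9% (equal) and 14.9% (uneven) at ICC 0. The uncorrected GEE alone gave 7.4% and 14.3%, so the second test adds only about half a percentage point.
- *The planned GEE will over-reject.* The article does not say whether a small-sample correction will be used, so the figures apply only if none is.
- *The baseline-adjusted models drop the clustering.* The text is silent on this, and such detail is commonly left out of an article.
- *The confidence interval will be too narrow.* The article names no interval for this test, although one built on the same standard error would share the fault.

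Choosing between t and Wilcoxon by observed normality, and the fact that the Wilcoxon test does not estimate a difference in mean change, are minor points with no measured harm.

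What the reply does not remove is that a patient-level test of the primary outcome is written into the plan of a provider-randomised trial. Pilot status lowers the stakes but does not make that test valid.

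**Conclusion.** The point holds in a limited form. The first-listed test of the primary outcome, carried over to HbA1c and diet, uses the wrong unit for the randomisation, and the article does not say whether it or the clustered GEE decides.

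The direction is certain for any positive ICC, but the size is not. It rests on an ICC and a spread of patients over providers that the article does not give. The true error of a nominal 5% t-test is about 6–10% for ICC 0.05 to 0.20 with equal clusters, up to about 13–15% at ICC 0.20 with uneven ones, and close to 5% near ICC 0.01. Switching to the GEE without a small-sample correction would replace one source of inflation with another.

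**What to change.** In the Statistical analysis section:

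1. Name one provider-clustered comparison of the change in steps/day as the sole primary analysis. Either the GEE on clinician with a small-sample variance correction and a t reference, or a t-test on the 20 provider means, would serve.
2. Delete the patient-level t-test/Wilcoxon step or label it descriptive, with no p-value used for inference.
3. Apply the same clustered method to HbA1c and diet.
4. State that the baseline-adjusted models keep the provider cluster term.

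The cost is wording, with no change to recruitment or data collection. Precision becomes slightly less favourable: with equal clusters and ICC 0, power for 2000 steps is about 52% on provider means against 55% for the patient-level t-test, and it falls to 45% at ICC 0.10. An unweighted t-test on provider means also gives each provider equal weight whatever the number of patients, so that choice should be stated.

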#### Patient consent

Once providers are enrolled, the EHR is queried to identify members of their panel with prediabetes. These patients are then contacted via telephone and invited to participate. A consent form is mailed home and discussed via a second phone call and verbal consent is obtained. A baseline survey is conducted on all patients (see Outcome section for specific domains). All patients are then mailed a pedometer (Omron HJ-170) to wear for one week and instructed to mail it back to the research team. A regular visit with their primary care provider was then scheduled for up to one month after the pedometer data were collected. On the night before the regular clinical visit, all patients were called to remind them of the visit, and the brief behavior-change goals-elicitation questionnaire was administered to intervention patients.

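### Neither planned test of the primary outcome adjusts for baseline steps/day, so an already underpowered pilot gives up precision it could have at almost no cost

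*Protocol article*

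**What the plan says.** The Outcome section defines the primary endpoint as the between-arm difference in the "change in mean steps per day at baseline and after six months (a difference of differences").

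The Statistical analysis section gives two tests of it. Arm differences in change "will be tested using a t-test or Wilcoxon test as appropriate, depending on the normality of the data". A GEE with clinician as cluster and an exchangeable correlation then tests the effect further, with "mean difference in steps/day as the outcome variable, and intervention group as the only explanatory variable". The same methods are carried over to HbA1c and diet.

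On baseline data, the Patient consent section states: "All patients are then mailed a pedometer (Omron HJ-170) to wear for one week". This happens before the first study visit. The Statistical analysis section adds: "Additional analyses accounting for baseline variables will be performed using generalized linear models". It does not say which baseline variables these are, or whether clinician clustering is kept.

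On size, the section plans a "sample size of 60 patients (30 intervention and 30 control"), says that "this provides us 49% power to detect a difference of the recommended physical activity change goal", gives the inputs as "2000 steps; standard deviation = 3649", and calls the trial underpowered.

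**The concern.** A change score subtracts the baseline with a fixed weight of one. A model with baseline as a covariate estimates that weight from the data. When the correlation between the two weeks of steps is below 1, the fixed weight is too large, and measurement noise and ordinary week-to-week variation in the baseline are carried into the outcome.

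This is a stated choice, not a detail left to a later document: the article says that arm is the sole explanatory variable. The first-named test adjusts for neither baseline nor clustering, the GEE adjusts for clustering only, and the additional models are committed to neither baseline steps nor clustering. No analysis in the article is therefore committed to both.

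What is at stake is precision, in a trial that says it has little. The contrast is also more sensitive to chance differences in baseline steps, and such differences are plausible when 20 providers are allocated by a random number generator with no stratification described.

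**Working it through.** **Inputs from the article (Statistical analysis):** 30 patients per arm, difference 2000 steps/day, SD 3649, stated power 49%. The article does not say whether 3649 is the SD of change or of steps at one time. It gives no alpha, sidedness or rho. Assumed here: two-sided alpha 0.05 and equal variances at baseline and six months.

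**1. The plan's own figure.** SE = 3649 × √(2/30) = 942, and 2000/942 = 2.123. Power is 56.5% by the normal formula and 55.1% by the noncentral t with 58 df. The stated 49% does not follow directly from the printed inputs. It appears with an unstated reduction: for example, 26 per arm gives 49.1% (t), and a design effect of 1.2 gives 49.1% (normal). It would also appear if 3649 were a single-time SD with rho between 0.4 (47.8%) and 0.5 (55.1%). Both 55% and 49% are used as starting points below.

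**2. Efficiency.** With SD s at each time:
- Variance of change: 2s²(1 − rho)
- Residual variance after baseline adjustment: s²(1 − rho²)
- Ratio, adjusted to change: (1 + rho)/2
- Information lost by using change: 1 − (1 + rho)/2 = (1 − rho)/2

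**3. Power, taking 3649 as the SD of change.** The adjusted residual SD is 3649 × √((1 + rho)/2), with 30 per arm and no clustering. The last column takes the stated 49% as the change-score power. Its noncentrality is 1.960 − 0.025 = 1.935, which is divided by √((1 + rho)/2) in the normal formula.

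| rho (assumed) | Information lost | Residual SD | Power from 55% | Power from 49% |
|---|---|---|---|---|
| 0.3 | 35% | 2942 | 73.5% | 67.0% |
| 0.5 | 25% | 3160 | 67.4% | 60.8% |
| 0.7 | 15% | 3364 | 62.0% | 55.5% |
| 0.9 | 5% | 3557 | 57.2% | 51.0% |

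**4. Power, taking 3649 as the SD at one time.** Change-score and adjusted power are then 42.3% and 59.0% at rho 0.3, 55.1% and 67.4% at 0.5, 76.9% and 83.2% at 0.7, and 99.7% and 99.8% at 0.9. The starting level changes greatly, but adjustment is better at each rho.

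**5. With clustering.** With 3 patients per provider (60/20), an assumed ICC of 0.05 (design effect 1 + 2 × 0.05 = 1.1), 18 df and 3649 as the SD of change, power goes from 48.2% to 59.9% (rho 0.5), 54.7% (0.7) or 50.2% (0.9). Taking 17 df, to pay for the covariate, lowers the adjusted figures by about 0.3 points.

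**6. Chance imbalance.** If the arms happen to differ by D steps at baseline, the change contrast shifts by about (1 − rho) × D, given that imbalance. For D = 1000 the shift is 500, 300 or 100 steps at rho 0.5, 0.7 or 0.9.

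**The case against.** The strongest defence is that the analysis fits the endpoint. The outcome is defined as a difference of differences, and the change-score comparison estimates exactly that without bias over randomisations. The trial is an openly underpowered pilot sized by resources, and it stays underpowered after adjustment unless rho is low or 3649 is a single-time SD. Baseline-adjusted analyses are also planned. All of this stands, and it makes the point one of efficiency, not validity.

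Several stronger readings are tempting, but the article does not support them:
- **A fixed loss of 15–25%.** That range is simply rho 0.5 to 0.7. Without a rho in the article, the loss can be given only as a range.
- **Biased estimation.** The shift in step 6 is conditional on a particular imbalance and averages to zero over randomisations.
- **Baseline discarded.** It is subtracted, with a weight that is usually not the best one.
- **The GEE as the designated primary model.** The t-test or Wilcoxon test comes first and the GEE is introduced as a further test. The omission applies to both.
- **Additional models that ignore clustering.** The article is silent, and a GEE can itself fit a generalized linear model. One can say only that no commitment is made.
- **Baseline steps in hand for everyone.** Collection is planned for all patients, but recruitment was ongoing and pedometers must be mailed back.
- **A need for a season covariate.** The article does not discuss season and shows no effect that differs by arm.

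One caution about the remedy also stands. The adjusted and change-score contrasts target the same quantity because randomisation makes expected baselines equal. If recruiting patients after provider allocation produced systematic differences, the two would diverge, and adjustment would not automatically be better.

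**Conclusion.** The point holds as a matter of efficiency. Both stated tests of the primary outcome leave out a strong covariate that the trial plans to measure in all patients before the first study visit. The planned estimator is valid. Under equal variances it loses (1 − rho)/2 of the information: 35% to 5% over rho 0.3 to 0.9. With 3649 as the SD of change, the unclustered gain is from 55% to between 57% (rho 0.9) and 67% (rho 0.5) power; from the stated 49%, it is to between 51% and 61%. These sizes rest on an assumed rho, a two-sided alpha of 0.05, and an SD whose meaning the article does not state. The direction of the gain does not depend on which SD is meant, and the gain becomes small only when rho is close to 1. It is worth correcting because it is nearly free, not because the planned analysis would mislead.

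**What to change.** Add baseline steps/day as a covariate to the clinician-clustered GEE, or to a mixed model with a clinician effect, and name that analysis as primary before outcome data are seen. The outcome may be either six-month steps or change: with baseline in the model, the arm coefficient is the same, and under randomisation it still estimates the between-arm difference in change. Treat HbA1c and diet the same way, each with its own baseline value. Keep the unadjusted change comparison as a supporting analysis. State that the additional baseline-variable models retain clinician clustering, and name their variables. Also say whether 3649 is the SD of change or of a single measurement, and which assumptions give 49%.

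The cost is a change of wording and about one degree of freedom. No new data, patients or procedures are needed.
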